### Exclusion criteria

Participants will be excluded if they have somatic co-morbidity causing reduced ability to work, primary large-scale alcohol or substance abuse, a legal guardian, forensic psychiatric arrangements, or if they do not give informed consent.

### Recruitment and randomisation

Eligible patients are informed about Sherpa, given the written information, and subsequently referred to Sherpa by their psychiatrists, nurse or social worker. A Sherpa employee calls the patient to make an appointment for inclusion and baseline interview. The assessor will interview the participants, but a Sherpa mentor will always attend the interview in order to manage the randomisation after the assessor has left and inform the participant about allocation. When a participant is included in the trial, central randomisation is performed when the Sherpa mentor calls the Copenhagen Trial Unit and gives the relevant participant information.

Randomisation is performed according to a computer-generated allocation sequence with a varying block size concealed from the investigators. The randomisation is stratified by a) four diagnoses (F31: Bipolar affective disorder; F30, F32-39: Affective disorders; F40: Phobic anxiety disorders; or F41: Other anxiety disorders), and b) two match groups (match group 2 or 3).

### Blinding

It is not possible to blind the participants, the Sherpa mentors, or career counsellors, practitioners and carers who deliver the intervention. However, they are strongly urged not to reveal the allocation to the rest of the research team. The assessor and research team will be blinded to the allocated intervention group throughout the entire trial period. Should blinding be violated, a second assessor will complete the follow-up interview. Furthermore, during statistical analyses, the two intervention groups will be coded as, for example, X and Y, and the code will not be broken until the research team has drawn two conclusions; one assuming X is the intervention group and Y is the control group, and one conclusion assuming the opposite.

### Interventions

#### The experimental intervention

Participants randomised to the Sherpa group will be offered IPS-MA in addition to treatment-as-usual (see description for the control group). A Danish protocol describing the IPS-MA method can be acquired by contacting the corresponding author. An English version is under construction. The IPS-MA method is based on eight principles: 1) Sherpa is the patient’s advocate, not an authority or a healthcare provider; 2) the process is led by the individual’s goals and focus is on patient resources; 3) assistance is flexible, without time limits, and responsive to the needs of the patient; 4) the goal is competitive employment or education, without pre-vocational training; 5) the belief is that returning to work is possible despite a mental illness, but therapeutic recommendations in terms of postponement are acknowledged; 6) liaison with healthcare and social workers ensures a coordinated service; 7) a meaningful and realistic career plan will be developed and evaluated continuously after job start; and 8) Sherpa is an interdisciplinary team, which will be reflected in the assistance of each individual.

Five basic services comprise IPS-MA:

1) *Individualised mentor support based on psychiatric knowledge*. Sherpa mentors all have a background as professionals in mental health services. In cooperation with the participant, the Sherpa mentor helps develop a plan of action in which resources and problems in social life as well as working life are clarified. The Sherpa mentor supports the participant in how to structure and manage everyday life, renew contact with friends and/or family, prepare important meetings and live a healthy everyday life with the disorder. The Sherpa mentors very often act as lay representatives for the participants at meetings at the local job centres or municipalities.

2) *Coordination of services provided by Sherpa or external providers*. Through their professional skills, Sherpa mentors help avoid lack of coordination and unnecessary waiting time and make sure that all available services are provided. Sherpa mentors have an assertive approach to mental health carers and social workers and thereby ensure that relevant information is distributed between services.

3) *Career counselling*. Professional career counsellors support participants in creating a realistic match between their competences and the demands of the job market. Participants will be given advice on how to write a curriculum vitae and job applications, on job seeking strategies, and help in practicing job interviews and negotiating employment contracts.

4) *Impartial help to clarify private economy* is offered by a consultancy firm, the Settlement [34], run by volunteers. The firm consists of two employees and a group of volunteers with professional backgrounds in economics, law and social counselling.

5) *Contact with employers* to help participants obtain jobs, and keep them.

Participants are provided with a Sherpa mentor who will be their mentor throughout the entire intervention period. The search for job or education will commence as soon as possible. Mentor support will continue for as long as needed after employment or education is started. During the first 6 months, the participant and mentor most often meet once a week for 1 to 1.5 hours on average. After 6 months the number of contacts varies and can be by telephone or email. The number and duration of contacts depend on the needs of the participant. Each mentor has a maximum caseload of 20 participants, half of which have been in Sherpa for more than 6 months.

#### Sherpa team

The Sherpa team is an interdisciplinary team, consisting of six mentors and two career counsellors. Sherpa mentors all have solid experience as health professionals in mental health services and include one nurse, two social workers and three occupational therapists. Career counsellors have worked as career counsellors, or with recruitment or human resources in the private business sector. Sherpa mentors and career counsellors work closely together and share offices.

#### Training and supervision

Newly appointed Sherpa mentors will have a 1-week introduction to working routines, and will attend a 2-day workshop introducing the IPS-MA method. Mentors with experience in the method will conduct the introduction. Team members are furthermore obliged to participate in annual refresher courses.

Team members will have monthly supervision provided by a trained psychologist.

#### The control group

Participants randomised to the control group will receive ‘treatment-as-usual’ as offered by the job centres in Denmark [35]. Services vary according to match group and the participant’s possibilities for social support. Participants receiving sickness benefits must attend their first meeting in the job centre within 8 weeks of sickness leave. Match group 2 participants attend follow-up interviews every 4 weeks, whereas match group 3 participants attend follow-up interviews every 3 months. Participants on social security will attend job-seeking interviews every 3 months.

Participants under the age of 30 have the right and obligation to participate in pre-vocational training after no more than 13 weeks of unemployment. Pre-vocational training has to last for at least 6 months. Young participants must not be without some sort of pre-vocational training for more than 4 weeks. Participants over the age of 30 have the right and obligation to participate in pre-vocational training after no more than 9 months of unemployment.

After an individual evaluation, job centres can offer certain pre-vocational training services: company internship programmes in public or private companies as well as in sheltered workshops, wage subsidy jobs, skill development and guidance, and mentor support (often offered by a colleague who helps the participant adapt to the new workplace regarding norms and social competences). Participants receiving sickness benefits can be provided with gradual return to employment, assistive tools, a personal assistant or reimbursement of sickness benefits to the employer from the first day of sickness leave [35].

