### Power and sample size

We have been unable to find data on how many people actually return to employment or education with traditional pre-vocational training after anxiety or an affective disorder in either the Danish or the national literature. Therefore, we have leaned towards the findings in OPUS, a programme in which young people with schizophrenia receive early intensive treatment for 24 months. In OPUS it was found that 40% returned to employment or education versus 32% in the control group ([name], personal communication). Based on this knowledge, we conservatively estimate that 30% will regain employment or education following traditional pre-vocational training.

Across a broad range of studies of severe mental illness and IPS versus traditional pre-vocational training, studies show that approximately 50% more of the participants in the IPS groups regain employment compared to the control groups [15]. We therefore expect to find that 50% more of the participants in the Sherpa group compared to the control group will regain employment or education, and have estimated the true difference in the experimental and control group to be 15%-points; hence, 45% of the participants in the Sherpa group will regain employment. To be able to reject the null hypothesis that the proportion of participants who regain employment or education in the experimental and control group is equal with a probability (power) of 80%, 162 participants will be required in each group (total 324). The Type I error probability associated with the test of this null hypothesis is 5%. We also estimated the sample size using a power of 90%. This resulted in a total of 434 participants (2 × 217). We therefore plan to recruit a minimum of 324 participants and, in order to reduce the risk of type II error, we will aim to recruit up to 434 participants, if possible, in the 2-year recruitment period. Power and sample size calculations have been made using the PS Power and Sample Size Calculations program version 3.0.14 [55,56].

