### Statistical analyses

Data analyses will be based on the intention-to-treat principle, which means that data will be included in the group to which the participant was randomised, regardless of intervention received. Data will be analysed using the IBM SPSS Statistics version 20 for Windows.

To assess homogeneity of the two groups at baseline, demographic data such as age, gender, marital status, education level, support (social benefits, social security and so forth), diagnosis and Match group at baseline will be presented.

Dichotomous outcomes will be analysed using logistic regression. For primary and secondary outcomes, an unadjusted analysis of the effect of the Sherpa method as an add-on to treatment-as-usual versus exclusively treatment-as-usual will be carried out, as well as an analysis adjusted for stratification variables (diagnosis and Match group). Multiple multivariate imputations will be used to impute a distribution of missing values.

Continuous outcomes will be analysed in a mixed model with repeated measurements. This model is based on the assumption that data are missing at random or missing completely at random [60].

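### Age partly governs when usual pre-vocational training must start, yet the adjusted analysis leaves it out; prespecifying it as a covariate is a small, free improvement.

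*Protocol article*

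**What the plan says.** The protocol article, under The control group, describes the services that job centres offer. For the young it says "Participants under the age of 30 have the right and obligation to participate in pre-vocational training after no more than 13 weeks of unemployment"; their training must last at least 6 months and gaps may not exceed 4 weeks. For the rest it says "Participants over the age of 30 have the right and obligation to participate in pre-vocational training after no more than 9 months of unemployment". The same section says that services also vary with match group and social support, and that what is offered follows an individual evaluation.

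Under Recruitment and randomisation, "The randomisation is stratified by a) four diagnoses" and by match group 2 or 3. Age is not a factor.

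Under Statistical analyses, the primary and secondary outcomes get an unadjusted analysis "as well as an analysis adjusted for stratification variables (diagnosis and Match group"). Age appears only in the baseline description, among "demographic data such as age, gender, marital status, education level" and similar items. Eligibility is limited to ages 18 to 60, so age must be known for everyone randomised.

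**The concern.** Two features of a participant affect the usual service in ways the article spells out: match group, which sets how often interviews take place, and age, which sets how soon pre-vocational training must begin. The first is stratified and adjusted for; the second is neither.

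Age could plausibly predict the primary outcome. Job centres may offer wage-subsidised jobs, and the Outcomes section counts such jobs as success. Days in employment or education are assessed at 12 months as well as 24, and the gap between 13 weeks and 9 months falls inside the first year. If age is prognostic, leaving it out has two consequences. A chance difference between arms in the share under 30 stays in both planned estimates, and the outcome variation that age explains stays in the error. The article also says nothing about what follows if the baseline table shows an age difference. Adding age at that point would be a data-driven choice.

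**Working it through.** **1. The plan's own figure.** Inputs from Power and sample size: "we conservatively estimate that 30% will regain employment or education following traditional pre-vocational training"; "hence, 45% of the participants in the Sherpa group will regain employment"; type I error 5%, taken as two-sided; power 80%; 162 per group. With pooled variance under the null and no continuity correction:

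n = [1.96·√(2·0.375·0.625) + 0.8416·√(0.30·0.70 + 0.45·0.55)]² / 0.15² = 162.3, so 163 per group.

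The article states 162, where power is 79.9%. At 90% power the formula gives 217, as stated. The sample size reproduces and does not depend on age.

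**2. Assumptions.** The document gives no age distribution and no relation between age and outcome. I take a share q under 30 of 0.3 to 0.5, and a difference δ in outcome probability between the age bands of 5 to 20 percentage points.

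**3. Chance imbalance in the share under 30.** SD = √(2q(1−q)/162).
- q = 0.3: √(0.42/162) = 0.051; 95% limit 1.96 × 0.051 = 10.0 points.
- q = 0.5: √(0.50/162) = 0.056; 95% limit 10.9 points.

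**4. Shift in the risk difference at that limit.** Shift = imbalance × δ.

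| δ | Shift, q = 0.3 to 0.5 |
|---|---|
| 5 points | 0.5 points |
| 10 points | 1.0 to 1.1 points |
| 20 points | 2.0 to 2.2 points |

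For scale, the planned difference is 15 points. Its standard error is √((0.21 + 0.2475)/162) = 5.31 points, a 95% half-width of 10.4 points.

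**5. Gain from adjusting.** Share of variance removed = q(1−q)δ² / 0.22875, where 0.22875 is the mean of 0.21 and 0.2475. Power is Φ(0.15/SE − 1.96), which is 80.6% without age.

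| q | δ | Variance removed | SE (points) | Power | Worth, of 324 |
|---|---|---|---|---|---|
| 0.3 | 5 points | 0.2% | 5.31 | 80.7% | under 1 |
| 0.4 | 10 points | 1.0% | 5.29 | 81.0% | about 3 |
| 0.4 | 20 points | 4.2% | 5.20 | 82.2% | about 14 |
| 0.5 | 20 points | 4.4% | 5.20 | 82.3% | about 14 |

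Over the whole range the gain is 0.1 to 1.7 points of power.

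**6. Check by simulation.** Logistic regression, 3,000 trials per setting, 162 per arm, q = 0.4.
- Type I error (30% in both arms), over age effects of 0, 10 and 20 points: 4.6 to 4.7% without age, 4.6 to 5.0% with age.
- Power without and with age: 78.5% and 79.1% (δ = 10 points); 79.6% and 81.1% (δ = 20 points). Monte Carlo error is about 0.7 points.

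A second simulation (6,000 trials per setting, q = 0.3 or 0.5) expressed the age effect as an odds ratio. Power rose by about 0.4 points at an odds ratio of 1.5, about 1 point at 2 and about 2.5 points at 3. Each 10-point imbalance moved the unadjusted risk difference by 0.7 to 2.6 points and the age-adjusted one by at most 0.2 points. A shift of 2.5 to 2.6 points per 10 points of imbalance implies an age effect of about 25 points. That lies beyond the range in step 5 and explains the higher top figure.

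None of these runs included diagnosis or Match group, and the mixed models for the secondary outcomes were not computed.

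**The case against.** The strongest reply is that nothing here is wrong. The adjusted analysis matches the randomisation, which is a standard choice, and further covariates are often left to an analysis plan that is not shown. The first half stands: there is no contradiction and no miscalculation. The second half carries less weight, because the article names the covariate set instead of leaving it open.

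Three stronger readings are tempting, and the document does not support them.

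- *That age sets the comparator.* It sets the latest start of one component and, for the young, the minimum length and maximum gap. Those over 30 may start earlier, and both bands are under the obligation by 9 months of unemployment, whereas the primary outcome is at 24 months. The Inclusion criteria describe match group 3 as unable to take part in pre-vocational training, so the age rule has little scope there. Match group itself is already stratified and adjusted for.
- *That the primary estimate is biased.* The Sherpa arm also receives treatment-as-usual, so the rule does not by itself separate the arms. A chance imbalance is covered by the standard error, and the test keeps its level.
- *That the effect must be shown in each age band.* IPS-MA aims at work or education without pre-vocational training, so the contrast could differ by band. But with 30 to 50% under 30, that band has about 49 to 81 per arm. The half-width is then 1.96·√(0.4575/49) = 19 points down to 1.96·√(0.4575/81) = 15 points, around a planned effect of 15. Such estimates cannot show whether the effect holds in both bands.

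It is also fair to say that the gain is small, and that in logistic regression adding a covariate does not shrink the standard error of the log odds ratio. The benefit appears as slightly higher power.

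**Conclusion.** The point holds as a free improvement, not as a defect. The planned analyses are valid without age. Adding it would raise power for the primary outcome by about 0.1 to 2.5 points. It would also largely remove a shift in the risk difference of about 1 to 2 points, for age effects of 10 to 20 points and a chance imbalance of about 10 points. These sizes rest on an assumed 30 to 50% under 30 and an assumed age effect of 5 to 20 points, or an odds ratio of 1.5 to 3. If age does not predict the outcome, nothing material is gained or lost: simulated power was 80.4% with and without it.

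**What to change.** Before outcomes by group are seen, name age as a covariate next to diagnosis and Match group in the adjusted logistic model for the primary outcome and in the mixed models for the secondary outcomes. State its form: an indicator for under 30 follows the service rule, and age in years can be added. Leave the stratification as it is, since splitting on age would double the 8 strata to 16. Make no age-band claim.

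The cost is one line of text and one or two model terms, with no new data and no more participants. At the planned rates there are about 162 × 0.30 + 162 × 0.45 = 121.5 events. The model would have at most seven terms besides the intercept (treatment, three for diagnosis, one for Match group, two for age), or about 17 events per term.

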### Participant withdrawal

Participants can choose to withdraw from the trial at any time during the intervention period, without it having any consequences for the treatment they will receive, but they will politely be reminded of the importance of their participation. Participants who choose to withdraw from the trial are asked to specify which aspects of the trial they withdraw from: participation in the experimental intervention, participation in the follow-up interviews, use of data collected at central registers, or complete withdrawal including use of already collected data.

### Fidelity

To ensure that the services provided by Sherpa are in concordance with the IPS-MA method, an independent investigator will monitor fidelity to the IPS-MA method twice during the first year of the intervention, and subsequently once every year. Fidelity will be monitored using the IPS-MA Fidelity Scale (unpublished, available through corresponding author) by interviewing participants, mentors, and career counsellors, observing team-meetings and meetings between mentor and participant, as well as examining the individual plans of action and the data management systems used. The IPS-MA Fidelity Scale was developed based on the IPS Fidelity Scale [36]. Core elements important to the IPS-MA method investigated are: caseload, mentors’ and career counsellors’ roles, interdisciplinary team with group supervision, individualised mentor support, development and evaluation of individual plans of action, coordination of services, providing career and economic counselling, focus on rapid search for ordinary employment or education, no time limitations, and individualised support for the participants and their employers, community-based services, assertive engagement and outreach.

### Assessments

Participants will be interviewed and asked to fill in questionnaires at baseline and at follow-up after 12 and 24 months. At baseline, socio-demographic information on education, income base, marital status, number of children and somatic disease will be collected.

To confirm the diagnosis, the Mini International Neuropsychiatric Interview (MINI) [37] is used at baseline. Baseline interviews will always be face-to-face, most often in the participants’ home. Participants will fill in questionnaires at home.

### Outcomes

The primary outcome is competitive employment (including being on rehabilitation benefits, flexible jobs, and wage-subsidised jobs) or education at 24 months. Information about employment and education will be extracted from the DREAM database [38]. The database is administered by The National Labour Market Authority and contains information on employment, sickness leave, and education eligible to state education grant, pre-vocational training, disability pension, social security, and sickness benefits.

Secondary outcomes are: 1) number of days of competitive employment or education; 2) level of symptoms assessed by the Hamilton Depression Scale (HAM-D6) [39,40]; 3) level of symptoms assessed by the Hamilton Anxiety Scale (HAM-A6) [39,41]; 4) level of functioning assessed by The Global Assessment of Functioning (GAF) [39,42,43]; and 5) level of health-related quality of life by The WHO-Five Well-being Index(WHO-5) [39]. Secondary outcomes are assessed after 12 and 24 months.

Exploratory outcomes are: competitive employment (including being on rehabilitation benefits, flexible jobs and wage subsidy jobs) or education at 12 months, re-assignment from Match group 2 or 3 to Match group 1, attending company internship programs in public or private companies as well as in sheltered workshops, and information extracted from the DREAM database. Manic symptoms are assessed by the Bech-Rafaelsen Mania Scale (MAS) [39,44]. Social performance regarding four domains (socially useful activities, personal and social relationships, self-care and disturbing and aggressive behaviour) is assessed by The Personal and Social Performance (PSP) [45,46]. The Sheehan Disability Scale [47] measures functional level regarding social relationships, work, spare time and family. Health-related quality of life in terms of psychological well-being is assessed by the WHO-5 [39,48] and empowerment by the Empowerment Scale [49]. The Changes Questionnaire [50] will be used to assess how motivated participants are as to seeking employment or education. The Client Satisfaction Questionnaire [51] assesses satisfaction with treatment and the EQ-5D (EuroQol) [52] assesses health-related quality of life. The latter of the two will be used in a future health-related cost-benefit analysis. All scales and questionnaires used for measuring outcomes are validated scales [37,39-47,49-52].

